## Abstract

**Background:**

The UN Convention on the Rights of Persons with Disabilities, and the reformed guardianship law in Germany, require that persons with a disability, including people with dementia in Alzheimer’s disease (PwAD), are supported in making self-determined decisions. This support is achieved through communication. While content-related communication is a deficit of PwAD, relational aspects of communication are a resource. Research in supported decision-making (SDM) has investigated the effectiveness of different content-related support strategies for PwAD but has only succeeded in improving understanding, which, although one criterion of capacity to consent, is not sufficient to ensure overall capacity to consent. The aim of the ‘spatial intervention study’ of the DECIDE project is to examine an innovative resource-oriented SDM approach that focuses on relational aspects. We hypothesise that talking to PwAD in their familiar home setting (as opposed to a clinical setting) will reduce the complexity of the decision-making process and enhance overall capacity to consent.

**Methods:**

People with a suspected or confirmed diagnosis of dementia in Alzheimer’s disease will be recruited from two memory clinics (*N* = 80). We will use a randomised crossover design to investigate the intervention effect of the decision-making place on capacity to consent. Besides reasoning capacity, which is part of overall capacity to consent and will be the primary outcome, various secondary outcomes (e.g., other aspects of capacity to consent, subjective task complexity, decisional conflict) and suspected moderating or mediating variables (e.g., meaning of home, demographic characteristics) will be assessed.

**Discussion:**

The results of the study will be used to develop a new SDM strategy that is based on relational resources for PwAD. If a change in location achieves the anticipated improvement in capacity to consent, future research should focus on implementing this SDM strategy in a cost-effective manner in clinical practice.

*Trial registration*: DRKS00030799.

**Supplementary Information:**

The online version contains supplementary material available at 10.1186/s12910-023-00905-0.

## Background

### Relevance

Article 12 of the UN Convention on the Rights of Persons with Disabilities (UN-CRPD, ratified by Germany in 2009) requires that people with disabilities should have access to the support they need to make legally valid decisions. The reform of the guardianship law in Germany (which entered into force on the January 1^st^, 2023) emphasizes the requirement to support the self-determination of people with disabilities.

The decline in the cognitive abilities of people with dementia in Alzheimer’s disease (PwAD) can result in them losing their capacity to consent and consequently their ability to make legal decisions that affect them [1, 2]. According to Grisso and Applebaum [3], the mental capacity to consent requires the ability to ‘understand’, ‘appreciate’, ‘reason’, and ‘express a choice’. PwAD lack the ability to ‘understand’ and ‘reason’ [4], while their ability to ‘appreciate’ and ‘express a choice’ are less impaired [2, 5, 6].

Previous research into supported decision-making (SDM) in PwAD has focused on the use of SDM strategies like keyword lists, elaborated plain language, and visualisation to compensate for deficits in verbal retrieval and improve a person’s understanding of information [7]. We consider SDM to be a communicative process and base our understanding of it on the combined communication model of Haberstroh et al. [8], in which the mentioned strategies support both verbal and non-verbal content aspects of communication. Poth et al. [9] have shown that such content-related SDM strategies, although leading to a significant enhancement in PwAD’s understanding of information, did not achieve a clinically relevant improvement in overall capacity to consent. The question facing us is therefore what else we can do to support decision-making processes in PwAD?

Besides verbal and non-verbal content aspects, the non-verbal relationship aspect is an important component of communication [8, 10]. Examples of these are feelings, mental states, and expressions of emotion [11]. Knebel et al. [10] showed that people with mild and moderate dementia also performed better in relationship aspects of communication than in content-related aspects.

From the viewpoint of environmental gerontology, decision-making is an interaction between characteristics of the person and the environment. Oswald and Wahl [12] postulated a framework that distinguishes between behaviour-driven ‘agency’ processes and experience-driven ‘belonging’ processes. As familiar places and objects provide a source of stability and self-continuity, particularly at a time of cognitive decline, Niedoba [13] highlights the importance of belonging for people in the transition to Alzheimer’s disease.

The current study will combine these findings and investigate an innovative SDM approach that focuses on the strengths of PwAD by supporting the relational aspects of communication and activating processes of belonging [14]. As part of the DECIDE project, the ‘spatial intervention study’ will investigate whether talking to PwAD in a highly familiar environment like their home enhances their capacity to consent. We expect the sense of belonging at home to reduce cognitive workload and the complexity of the decision-making process.

### Study aims

The *primary aim* of the spatial intervention study is to demonstrate that *home is a better place and more amenable for complex decision-making processes than an unfamiliar place* like a memory clinic, and that it improves the capacity to consent required (in this case) to create an advance directive. We assume that being at home, where the sense of belonging is strong, lessens subjective task complexity, decisional conflicts, and anxiety, and consequently increases rated capacity to consent. Our *secondary aim* is therefore to explore whether the anticipated influence of the place a decision is made on subjectively perceived task complexity, decisional conflicts and anxiety actually exists and, if so, whether it is affected by the extent of a person’s sense of belonging at home. We will also explore the influence of further potential confounders, moderators, and mediators.

## Methods

### Participants

Participants will be recruited from two outpatient memory clinics (University Hospital Frankfurt, Germany; Klinikum Siegen, Germany). We plan to recruit *n* = 40 participants at each location, for a total of *N* = 80 participants (for calculation see below). Recruitment is terminated either after reaching the optimal sample size or by the end of the project duration (planned for March 31st, 2024).

We will include patients with a suspected or confirmed diagnosis of dementia in Alzheimer’s disease (F00.1), or a mixed type of dementia in Alzheimer’s disease (F00.2). The neuropsychological diagnosis will be the determining factor in differentiating between Alzheimer’s disease and other types of dementia. The responsible neuropsychologists will analyse the cognitive profiles of potential participants and discuss complex cases with experts from their research group where appropriate. Since capacity to consent to study participation may be an issue, the inclusion process will be based on the decision tree for the inclusion of *non-consenting* individuals in medical research [15]. This will permit us to include participants whose capacity to consent is questionable.

Exclusion criteria are severe dementia (confirmed clinical diagnosis or MMSE-score < 10), delirium, intellectual disability, severe mental illness (e.g., clinical diagnosis of severe depression or GDS-score > 10), lack of capacity to consent to medical research with simultaneous inability to participate in SDM involving a relative or proxy, no assent by the patient, uncompensated and pronounced sensory deficits, or persons whose knowledge of the German language is insufficient to understand the study documents and/or an interview. They will also be excluded, if they have taken part in the intervention phase of the first study of the DECIDE project [16]. There are no restrictions regarding concomitant interventions.

### Intervention

The intervention lies in making decisions at home, which is a place where patients have a strong sense of belonging, as opposed to a memory clinic where they do not. It is important to note that our focus is on capacity to consent. Its object, the creation of an advance directive, is only an example of a relevant and complex decision-making situation. The offer to participate in advance care planning (ACP) and the ACP itself are *not* part of the intervention.

### Study design

We will use a randomised AB/BA crossover design to study the effect of the spatial intervention ‘decision-making place: home vs. memory clinic’ on capacity to consent to an advance directive. Each participant will undergo one session at the memory clinic and one session at their home. The decision where the first session will be conducted will be made randomly for each PwAD, and stratified by site. The crossover design will further permit us to examine the presence of substantial period and carryover effects.

### Procedure

#### Data collection

The procedure of the spatial intervention study is presented in Fig. 1*.* Patients fulfilling the inclusion criteria will be asked whether they wish to participate at their final appointment at the memory clinic (T0). If they agree, the physician will assess suspected moderators, mediators and confounders including demographic variables, severity of dementia and depression, perceived sense of belonging to home, need for autonomy in medical decisions and health literacy (see Table 1). Afterwards, two further appointments will be made. Patients will be assigned to one of the two groups by using site specific randomisation lists with two levels (i.e., the order of visits) and a final block size of 4. These lists were created using R and the R package blockrand [17, 18]. At the beginning of each session (T1 & T2), the research physician will assess the capacity to consent of the individual to complete an advance directive, as well as subjective task complexity, decisional conflicts, and anxiety in the decision-making situation (see Table 1). As the decision-making situation should be as realistic as possible and also be of benefit to the participants, they will all have the chance to take part in ACP following the assessment. They can decide whether to create an advance directive with the help of the study physician, or whether to gather information on a possible care directive or lasting power of attorney. It is also possible to decide against ACP. The ACP process will be divided between the two sessions to avoid overload.

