### Statistical methods

#### Analysis population

Since our intervention consists in making a decision at two different places in a certain order, the only possible reason why the intervention might not conform to the study protocol is – apart from missing data issues – that the sequence of the places is swapped. If this occurs, it will be due to an organisational error, i. e. completely at random. This means the patient can be analysed with the sequence group that corresponds to his or her actual sequence without generating any bias. Apart from this, as the appointments for the interviews involve two persons (study nurse and physician) checking the correct sequence independently, we consider such an error highly unlikely. Hence, the analysis population will be the “as treated” population.

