#### Statistical analysis

A linear mixed model with place, period, and interaction of place and period as fixed effects and patient as a random effect will be used to analyse the primary endpoint. We will check for carryover by testing the interaction between place and period. If there is no significant interaction effect, differential carryover can be neglected. Otherwise, statistical analysis will be stratified by period, whereby the main analysis will be restricted to the first period, and data from the second period will be used for sensitivity analysis.

An exploratory investigation of the impact of the place the decision is made on subjective task complexity, decisional conflicts and anxiety will be based on a model that is analogous to the main analysis.

Furthermore, both linear mixed models will be extended to include an exploratory analysis of potentially confounding, moderating, and mediating variables.

The relationship between the place the decision is made, and the other secondary endpoints will be explored by conducting two-sample comparisons between the sequence groups in a two-step procedure based on Wilcoxon-Mann–Whitney tests, consisting of a pretest for differential carryover and a main test for the location effect. This is essentially equivalent to the mixed model approach but assumes no particular probability distributions and does not permit inclusion of covariates. If the pretest is significant, the main test will only be performed on data from the first period.

The features of the patient sample will be summarised descriptively. Absolute and relative frequencies will be used for categorical variables, and mean, standard deviation, minimum, maximum, and quartiles for metric variables.

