#### Informed consent and assent

At their final appointment at the memory clinic, the study physician will tell the participants about the study and answer any questions they have. If participants agree to participate, he will obtain their written informed consent. The information provided to participants and the informed consent form are available on request.

Since participants have a suspected or final diagnosis of dementia in Alzheimer’s disease, their capacity to consent to study participation may be an issue. Following German AWMF S2k guidelines to medical procedures, we will support the participants as far as possible. If their capacity to consent is questionable, consent by proxy will be an option but nonetheless require the patient’s assent. Patients that neither consent nor agree to consent by proxy will be excluded from study participation.

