## Limitations

It will be challenging to recruit a sample of PwAD of sufficient size. However, as our study physicians provide regular care in a memory clinic, we have good access to the target population and to potential participants. Nevertheless, PwAD have limited capacities and would be required to attend two further appointments in addition to the three regular appointments at the memory clinic. As has frequently been the case in the past, this may result in our recruiting less impaired people because they have more resources and thus agree more often to study participation.

Moreover, it will not be possible to blind the study physicians to the intervention effect because they are part of the research team, and a change in location is an obvious intervention. We therefore risk bias in the assessment of capacity to consent if the study physicians unconsciously give participants higher scores either at home or in the clinic. To minimise the risk of bias, our physicians will be made aware of the possibility and use a standardised instrument for the assessment of capacity to consent.

Furthermore, the standardised assessment of capacity to consent to an advance directive using the CAT-AD is known to be more conservative than a clinical assessment [35]. Grisso and Applebaum [36] conclude that the assessment of the capacity to consent should not be wholly based on the instrument, and a sum score for overall capacity to consent should not be calculated. In our study, the final decision on whether a person is able to consent will therefore be made by using cut-off criteria at a subscale level.

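### A single block size of 4 per site lets an enrolling physician deduce up to one third of sequences, leaving the carryover test and first-period fallback open to selection bias

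*Protocol article*

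**What the plan says.** **Assignment.** Under Study design, the place of the first session is "made randomly for each PwAD, and stratified by site". Under Data collection, patients are assigned from "site specific randomisation lists with two levels (i.e., the order of visits) and a final block size of 4". The Participants section plans "40 participants at each location", which makes ten blocks of 4 per site. Under Data management, the lists are made by a committee whose members take no part in data collection.

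**Who sees what.** At T0, "the study physician will tell the participants about the study and answer any questions they have" and also obtains consent (Informed consent and assent). A research physician scores capacity at T1 and T2 (Data collection). The Analysis population section describes "two persons (study nurse and physician) checking the correct sequence independently". The study physicians are lead investigators, collect the data and sit on the Trial Management Committee, which works out design and procedure (Trial monitoring; Principal and lead investigators). The Limitations section concedes that "it will not be possible to blind the study physicians to the intervention effect because they are part of the research team".

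**Analysis.** The primary model uses both periods. If the place-by-period interaction is significant, "the main analysis will be restricted to the first period" (Statistical analysis). The sections on missing data and sample size also allow a restriction to first observations if too many patients are seen only once.

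**The concern.** With a known block size, past assignments reveal some future ones. The last assignment in a block of 4 is always determined, and the last two are determined when the first two agree. Keeping the list itself hidden does not prevent this, because the order of visits is visible to those who run them.

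A crossover removes most of the consequence but not all of it. In an AB/BA design the place-by-period interaction is estimated from the difference between sequence groups in the patients' totals. The first-period place effect is likewise a plain comparison between sequence groups. Both depend on the two groups being alike at entry. If more impaired patients tended to enter one order, the same imbalance could trigger the fallback and then bias its result.

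**Working it through.** The article gives no figure for predictability, so there is none to reproduce. As a check on the planning inputs used below: a 20% carryover lowers the two-period contrast by 10%, so 0.582 × 0.9 = 0.524. With 80 observations per place and two-sided α of 5%, power is 90.9%, which agrees with the stated 90% for 80 patients.

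**Inputs from the article:** block size 4, two sequences, 40 patients at each of two sites, standardised effect 0.582, score SD 2.83. **Assumed:** one constant block size and 1:1 allocation (the natural reading, not stated in words).

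**1. Assignments known with certainty.** There are 6 equally likely arrangements of a block.
- Positions 1 and 2: never determined.
- Position 3: determined in 2 of 6 arrangements.
- Position 4: always determined.
- Share = (0 + 0 + 1/3 + 1)/4 = 1/3, that is 13.3 of 40 per site and 26.7 of 80.

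**2. Best-guess rate** (guess the sequence with more places left): (1/2 + 2/3 + 2/3 + 1)/4 = 0.708, against 0.5 for unrestricted assignment.

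**3. First-period bias if every known assignment is steered.** Let δ be the shift in SD units, upward for one sequence and downward for the other (an assumption; nothing in the article gives it). One third of each group is shifted, so bias = 2δ/3. Type I error is from the noncentral t with 40 per group, df 78 and noncentrality bias × √20.

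| δ (SD) | Bias (SD) | Share of 0.582 | Score points (× 2.83) | Type I error, first-period test |
|---|---|---|---|---|
| 0 | 0 | 0% | 0 | 5% |
| 0.10 | 0.07 | 11% | 0.19 | 6.0% |
| 0.25 | 0.17 | 29% | 0.47 | 11.4% |
| 0.50 | 0.33 | 57% | 0.94 | 31% |

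**4. The whole two-step rule.** Simulated with no true place effect, 40 patients per sequence, the interaction tested at 5%, within-patient correlation 0.2 to 0.5, and steering on a stable patient trait:
- δ = 0: fallback triggered in 5% of runs; overall type I error about 7%.
- δ = 0.25: fallback triggered in about 15%; overall about 12%.
- δ = 0.50: fallback triggered in about 40%; overall nearly 30%.
- Two-period test alone: about 5% in every case.

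The 7% without any steering comes from the two-step rule itself, not from the blocks.

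**5. Effect of varying the block size** (simulated lists of 40; the guesser knows the set of sizes but not the order drawn):

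| Block sizes | Known with certainty | Best guess correct |
|---|---|---|
| 4 only | 33% | 71% |
| 4 and 6 | about 6% | about 69% |
| 2, 4 and 6 | about 4% | about 70% |

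**The case against.** The strongest reply is that the exposure is theoretical.

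- **Knowledge.** One third is a ceiling. It needs a person who knows the block size, follows every assignment at the site in order and knows where each block begins. The article names physicians and neuropsychologists in the plural and does not say that one of them sees everything.
- **Opportunity.** The neuropsychological diagnosis decides inclusion, questionable capacity is handled through proxy consent with assent rather than exclusion, and T0 is the final routine diagnostic appointment. This leaves limited room to steer.
- **Motive.** Every patient gets both places and the same offer of advance care planning.
- **Consequence.** The main analysis is within patient, the authors expect no substantial carryover, and the first-period analysis is conditional. MMSE, GDS, age and education are recorded at T0, so an imbalance in them would be visible.
- **Convention.** Blocks of 4 within site are common and keep the sequences balanced at 40 per site.

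All of this stands, and it limits the point to a precaution. It does not remove the point. The fallback and its trigger are written into the plan, both compare sequence groups, and a check of measured T0 variables cannot cover unmeasured ones.

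A reader might infer that allocation is not concealed at all. The article does not support that. It describes assignment after the patient's agreement and the T0 assessment, and lists made by people outside data collection. Who holds the lists is a detail that an article may leave to the full protocol.

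**Conclusion.** The concern holds in a limited form. Under the natural reading of the block size, up to one third of sequences could be deduced with certainty by a physician who tracks assignments. This leaves the carryover test and the first-period fallback open to selection bias. The size of any bias depends on steering, for which the article gives no evidence: with none, there is none. The 0.17 SD and the rise from about 7% to about 12% assume that every deducible assignment is steered by 0.25 SD, and so lie at the upper end for that shift.

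A reader might go further and conclude that the block size undermines the trial's primary result. The article does not support this: the primary analysis uses both periods, and its place contrast hardly depends on who enters which sequence. This is a worthwhile improvement, not a defect that threatens the main analysis.

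**What to change.** For remaining patients, generate new lists within each site with randomly varying block sizes (for example 4 and 6, or 2, 4 and 6) and do not disclose the sizes to the sites. Start them once the block in use at the site is complete. Have the Data Management Committee hold the lists and release each sequence after consent and T0. The order of steps already described is close to this, so the new elements are the varied sizes, their non-disclosure and the release by that committee.

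The gain is in certain knowledge, from 33% to about 4–6%. The fix should not be presented as making assignments hard to guess, since the best-guess rate hardly changes.

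The cost is new lists, which the R package already in use can produce, and one message per patient. The possible end imbalance between sequences grows slightly, to at most 3 per site (half the largest block). Even 43 against 37 overall would raise the variance of a between-group comparison by only about 0.6%: (1/43 + 1/37)/(2/40) = 1.006.
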